#### **Incidence of Escalation/Reduction of Background Immunosuppressant Therapy:**

The background treatment regimen is collected at each of the follow up time points. Data on second line immunosuppressants is also collected (ciclosporin, tacrolimus, levamisole, mycophenolate mofetil, mycophenolate sodium, azathioprine, cyclophosphamide and rituximab). The background treatment regime is categorised into the following four categories:

1. No long-term alternate day prednisolone or other long-term immunosuppressive therapies
2. On long-term alternate day prednisolone only
3. On both long-term alternate day prednisolone and other long-term immunosuppressive therapies
4. On other long-term immunosuppressive therapies only

The background treatment regimen and second line immunosuppressant information will be used in the following way to calculate escalation/reduction of background immunosuppressant therapy:

*Escalation will be computed based as per the following criteria –*

- If a patient is in category 1 from the background treatment regime at previous visit and then at a following time-point is in category 2, 3 or 4 of the background treatment regime then this is considered as an escalation.
- If a patient is in category 2 from the background treatment regime at previous visit and then at a following time-point is in category 3 or 4 of the background treatment regime then this is also considered as an escalation.
- If a patient is in category 4 from the background treatment regime at previous visit and then at a following time-point is in category 3 of the background treatment regime then this is also considered as an escalation.
- If the participant is not on cyclophosphamide or rituximab at previous visit but are then given cyclophosphamide or rituximab at the following time-point then this is also considered as an escalation.
- If participant has an addition of any immunosuppressant (e.g. addition of ciclosporin) in between follow up visits then this is considered an escalation.
- If the participant has a change in medication from Levamisole to either Tacrolimus, Ciclosporin or Mycophenolate then this is also considered as an escalation.

*Reduction will be computed based as per the following criteria –*

- If a patient is in category 3 from the background treatment regime at previous visit and then at a following time-point is in category 4, 2 or 1 of the background treatment regime then this is considered as a reduction.
- If a patient is in category 4 from the background treatment regime at previous visit and then at a following time-point is in category 2 or 1 of the background treatment regime then this is also considered as a reduction.
- If a patient is in category 2 from the background treatment regime at previous visit and then at a following time-point is in category 1 of the background treatment regime then this is also considered as a reduction.
- If participant on an immunosuppressant (except cyclophosphamide or rituximab) at one time point, but is no longer on it at the following time point then this is also considered as a reduction.

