#### **4.9 Treatment of relapse**

Relapses should be treated in accordance with the ISKDC relapse regimen. Prednisolone should be commenced at a dose of 60mg/m^2 daily (maximum dose 80mg) until the urine has been negative or trace for three consecutive days, then reduced to 40mg/m^2 (maximum dose 60mg) on alternate days for four weeks (14 doses). A subsequent tapering dose can be used at the individual physician's discretion.

**Where relapse therapy is commenced, long term maintenance prednisolone therapy (e.g. 10mg on alternate days) is discontinued. Where relapse occurs whilst the child is receiving the six day course of study drug, this should also be discontinued. Once the relapse regimen has been completed, long term maintenance prednisolone therapy may be recommenced at any dose at the PI's discretion.**

**Background immunosuppressive therapy other than prednisolone e.g. ciclosporin, mycophenolate mofetil, levamisole etc. should be continued unchanged throughout the relapse treatment period.**

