#### **4.10 Escalation of background immunosuppressive therapy**

Subjects will only undergo intensification of background immunosuppressive therapy (i.e. the addition of a new immunosuppressive agent) where there are two or more relapses of their nephrotic syndrome (URTI-related or unrelated) in any six month period or where there are unacceptable adverse effects of prednisolone or other therapy. These subjects will remain under follow-up, though intensification of immunosuppressive therapy is an important study secondary endpoint. Similarly immunosuppressive therapy will only be discontinued where there is freedom from relapse for at least six months or where there are unacceptable adverse effects of therapy.

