### **4.23.2 Secondary endpoints/outcome measures:**

Rate of URTI-related relapse of nephrotic syndrome (relapses per year)

Rate of relapse (URTIs-related and non URTIs-related) of nephrotic syndrome (relapses per year)

Cumulative dose of prednisolone (mg/kg and mg/m^2) received over the 12 month study period

Incidence of SAEs

Incidence of adverse effects of prednisolone including assessment of behaviour using the Achenbach Child Behaviour Checklist

Incidence of escalation of background immunosuppressive therapy (e.g. addition of ciclosporin, tacrolimus, cyclophosphamide etc.)

Incidence of reduction of background immunosuppressive therapy (i.e. cessation of long term maintenance prednisolone therapy)

Quality of life using the CHU-9D, EQ-5D and PedsQL

Cost per relapse of nephrotic syndrome

Cost per QALY gained

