### **9.6. Analysis methods – secondary outcomes**

The number of participants experiencing any relapse (i.e. both URTI-related and non URTI-related relapses), the number of participants having an escalation of background immunosuppressant therapy and the number of participants having a reduction of background immunosuppressant therapy will be presented and analysed as per the primary outcome measure.

The rate of URTI-related relapses and rate of any relapse will be presented in the first instance as numbers of participants who have a relapse with the respective percentage, and in the second instance as a median and IQR. An adjusted incidence rate ratio with 95% confidence interval will be estimated using a Poisson regression model. An offset for the length of time the participant was in the trial will be included in the model. Statistical significance of the treatment group parameter will be determined from the p-value generated by the model.

The cumulative dose of prednisolone received over the 12 month period will be presented as means with standard deviations and ranges. Adjusted mean differences along with 95% confidence intervals will be estimated using a linear regression model. Statistical significance of the treatment group parameter will be determined from the p-value generated by the model.

Adverse effect data will be tabulated at each time point (3, 6, 9 and 12 months) with statistical significance determined by a chi-squared or Fisher's exact test (as appropriate). We will also assess whether or not each adverse event occurred over the whole trial period by assessing all the 3, 6, 9 and 12 month data collectively.

Quality of life measures are taken at multiple time points, as is the Achenbach Behaviour Checklist Scores. Means and standard deviations will be summarised at each time point. Data will be analysed using mixed effect repeated measures models with the minimisation variable and the baseline questionnaire score included in the model as covariates. Time will be included as a continuous variable in the model. In the initial model, a treatment by time cross-term will be included in the model. If this is not significant, it will be considered that the treatment effect

is constant over time, and models without the treatment by time cross-term will be fitted. Adjusted mean differences between groups will be presented alongside the respective 95% confidence interval.

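### SAP 9.4 scores a levamisole switch as both an escalation and a reduction, which puts treatment intensifications into the reduction outcome and can dilute that comparison

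*Combined protocol and SAP*

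**What the plan says.** SAP 9.4 sorts background therapy into four categories: 1 none, 2 maintenance prednisolone only, 3 prednisolone plus another agent, 4 other agents only. It then gives one list of escalation rules and a separate list of reduction rules.

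- Last escalation rule: "If the participant has a change in medication from Levamisole to either Tacrolimus, Ciclosporin or Mycophenolate then this is also considered as an escalation".
- Last reduction rule: "If participant on an immunosuppressant (except cyclophosphamide or rituximab) at one time point, but is no longer on it at the following time point", this counts as a reduction. The bracketed drugs are the only exemptions.
- General addition rule: "If participant has an addition of any immunosuppressant (e.g. addition of ciclosporin) in between follow up visits then this is considered an escalation".
- A child in category 2 who later "is in category 3 or 4 of the background treatment regime then this is also considered as an escalation".

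Neither list refers to the other, and there is no precedence or net-change rule. In SAP 9.6, escalation and reduction are separate participant-level outcomes: "the number of participants having a reduction of background immunosuppressant therapy will be presented and analysed as per the primary outcome measure". SAP 9.10 confines sensitivity analyses to the primary outcome.

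The protocol defines the terms in three places. Section 4.10 describes "intensification of background immunosuppressive therapy (i.e. the addition of a new immunosuppressive agent". Section 4.23.2 lists "Incidence of reduction of background immunosuppressive therapy (i.e. cessation of long term maintenance prednisolone therapy". Secondary objective vi in the Synopsis is wider and names stopping ciclosporin as an example of reduction.

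**The concern.** A child moved from levamisole to tacrolimus has had treatment stepped up. Under the SAP that child also counts as a reduction, because levamisole is no longer taken. Objective vi treats reduction as a benefit of active treatment, so an event that usually signals the opposite enters the numerator.

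The error need not be balanced between groups. Protocol 4.29 reasons that, if prednisolone works, placebo children relapse more and are intensified more. False reductions would then collect in the group expected to have fewer true ones, and the difference would shrink.

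The timing matters too. SAP 9.4 has the Trial Statistician derive all responses, and SAP 5.6 says that person has been unblinded for the interim analyses. A gap in the rules should not be left to be settled case by case by someone who knows the allocation.

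**Working it through.** **1. Figures in the plan.** The documents give no rate for escalation, reduction, levamisole use or switching, so there is no planned figure to reproduce for these outcomes. The sample size rests on the primary outcome alone: 50% against 32.5%, 80% power and two-sided 5% give 124 per group, or 248 (stated 250), and 250/0.70 = 357.1 (stated 360). It reproduces and is not touched by this point.

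**2. Which changes meet both definitions.** Take maintenance prednisolone yes or no, combined with no other agent or one of five (ciclosporin, tacrolimus, levamisole, mycophenolate, azathioprine). That is 2 × 6 = 12 states and 12 × 11 = 132 ordered changes.

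- Levamisole to ciclosporin, tacrolimus or mycophenolate: 3 drugs × 4 prednisolone patterns = 12 changes. All 12 meet an escalation rule and a reduction rule. Nine are reductions through the last reduction rule alone; the other three also stop maintenance prednisolone and so meet the category 3-to-4 rule as well.
- All agent swaps: 5 × 4 ordered pairs × 4 prednisolone patterns = 80. The last reduction rule catches every one. If a swap also counts as an addition, all 80 score twice. If it does not, 29 do: the 12 above plus 17 other swaps in which prednisolone is started in the same interval (category 4 to 3).
- A category 2-to-4 move scores as an escalation only, although it stops maintenance prednisolone, which Protocol 4.23.2 calls a reduction.

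**3. Effect on the reduction comparison.** Let r be the true reduction rate, e the escalation rate, and s the share of escalations that are switches; A is active, P placebo. All three are assumptions. If switching is independent of true reduction, the recorded rate is 1 − (1 − r)(1 − e·s), and

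recorded difference = (rA − rP) − s × [(1 − rP)·eP − (1 − rA)·eA].

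For rA = 15%, rP = 10%, eA = 20%, eP = 30%: 0.05 − s × (0.90 × 0.30 − 0.85 × 0.20) = 0.05 − 0.10·s. If instead no child has both events, the difference is (0.15 + 0.20·s) − (0.10 + 0.30·s), again 0.05 − 0.10·s. At s = 25% that second form records 20% against 17.5%.

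| True reduction A / P | Escalation A / P | True difference | s = 10% | s = 25% | s = 50% | s at which the difference is zero |
|---|---|---|---|---|---|---|
| 15% / 10% | 20% / 30% | 5 | 4.0 | 2.5 | 0.0 | 50% |
| 30% / 20% | 25% / 40% | 10 | 8.6 | 6.4 | 2.8 | 69% |
| 30% / 20% | 20% / 30% | 10 | 9.0 | 7.5 | 5.0 | 100% |
| 20% / 15% | 25% / 40% | 5 | 3.6 | 1.5 | −2.0 | 36% |
| 20% / 15% | 20% / 30% | 5 | 4.1 | 2.6 | 0.3 | 53% |

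Differences are in percentage points. In the second row, with 125 per group, power is 45% under correct coding and 33%, 19% and 6.5% at the three switch shares.

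**4. How large s could be.** Protocol 4.2 expects roughly even numbers in the four background groups, so about half the children start with no second-line agent and their first escalation cannot be a switch away from one. With equal escalation rates across groups, s = 50% would need almost every escalation in the other half to be a switch. Switches from levamisole alone can occur only in children taking it.

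**The case against.** The strongest reply is that the reach is narrow, and much of it stands.

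- A reader might infer that both outcomes are misclassified. The levamisole switch does not show that: counting it as an escalation matches Protocol 4.10. Only the reduction coding fails.
- A reader might infer that any swap scores twice. That depends on reading a replacement as an addition. If it were one, the separate levamisole rule would be redundant, which suggests that addition means add-on. The narrower reading does not rescue the reduction outcome, because the last reduction rule still counts the dropped agent.
- A reader might infer that the effect on reductions is lost or reversed. The documents give no rates. Across the assumed scenarios the difference reaches zero only when 36% to 100% of escalations are switches, and step 4 shows why a high share is hard to reach.
- A reader might infer that relapses themselves create false changes, since under Protocol 4.9 "Where relapse therapy is commenced, long term maintenance prednisolone therapy (e.g. 10mg on alternate days) is discontinued". A visit during a relapse course could record a lower category and the next visit a return. Whether it does depends on how sites record background regimen at that time, which the documents do not show. The frequency cannot be determined.
- It could be said that the reduction rules fit the Synopsis objective, which covers stopping ciclosporin. They do fit it for a drug stopped outright. Nothing in that objective covers a drug stopped because another replaces it.

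**Conclusion.** The defect is real and follows from the SAP's own text: a switch from levamisole to tacrolimus, ciclosporin or mycophenolate is scored as both an escalation and a reduction, and nothing later in the SAP resolves it. The reduction coding is wrong and contaminates one secondary outcome.

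The likely consequence is dilution. Under the base assumptions a true 5-point difference is recorded as 4 to 2.5 points when 10% to 25% of escalations are switches, and as zero at 50%. The direction rests on placebo children being intensified more often, which Protocol 4.29 expects only if prednisolone works. The size rests wholly on assumed rates. The primary outcome and the sample size stand.

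**What to change.** Amend SAP 9.4 and the derivation code before database lock.

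1. In any visit interval in which a stopped agent is replaced by another, score no reduction under any reduction rule. Changing the last rule alone is not enough, because the three levamisole switches that also stop maintenance prednisolone still meet the category 3-to-4 rule. Protocol 4.23.2 would call that stop a reduction, so the override should be stated as deliberate.
2. Keep the levamisole switch as an escalation.
3. State whether other like-for-like swaps count as an addition or are tabulated separately as switches.
4. Give category 2-to-4 moves one stated class.
5. Reconcile the definition of reduction across the Synopsis objective, Protocol 4.23.2 and SAP 9.4.
6. As a secondary point, state that a temporary stop of maintenance prednisolone during a relapse course is not a change of background regimen for this derivation.

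Items 1 to 5 cost wording and code only, as drug histories are already collected. Item 6 also uses relapse dates and may need some judgement: SAP 9.4 notes that part of the prednisolone dosing is free text and that some start or stop dates are missing.

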### **PedsQL for ages 2-4 years**

The PedsQL response scales are coded as follows:

#### Physical Functioning (problems with...)

- Walking: Never=100, Almost Never=75, Sometimes=50, Often=25, Almost Always=0

- Running: : Never=100, Almost Never=75, Sometimes=50, Often=25, Almost Always=0
- Participating in active play or exercise: Never=100, Almost Never=75, Sometimes=50, Often=25, Almost Always=0
- Lifting something heavy: Never=100, Almost Never=75, Sometimes=50, Often=25, Almost Always=0
- Bathing: Never=100, Almost Never=75, Sometimes=50, Often=25, Almost Always=0
- Helping to pick up his or her toys: Never=100, Almost Never=75, Sometimes=50, Often=25, Almost Always=0
- Having hurts or aches: Never=100, Almost Never=75, Sometimes=50, Often=25, Almost Always=0
- Low energy level: Never=100, Almost Never=75, Sometimes=50, Often=25, Almost Always=0

#### Emotional Functioning (problems with...)

- Feeling afraid or scared: Never=100, Almost Never=75, Sometimes=50, Often=25, Almost Always=0
- Feeling sad or blue: Never=100, Almost Never=75, Sometimes=50, Often=25, Almost Always=0
- Feeling angry: Never=100, Almost Never=75, Sometimes=50, Often=25, Almost Always=0
- Trouble sleeping: Never=100, Almost Never=75, Sometimes=50, Often=25, Almost Always=0
- Worrying: Never=100, Almost Never=75, Sometimes=50, Often=25, Almost Always=0

#### Social Functioning (problems with...)

- Playing with other children: Never=100, Almost Never=75, Sometimes=50, Often=25, Almost Always=0
- Other kids not wanting to play with him or her: Never=100, Almost Never=75, Sometimes=50, Often=25, Almost Always=0

- Getting teased by other children: Never=100, Almost Never=75, Sometimes=50, Often=25, Almost Always=0
- Not able to do things that other children his or her age can do: Never=100, Almost Never=75, Sometimes=50, Often=25, Almost Always=0
- Keeping up when playing with other children: Never=100, Almost Never=75, Sometimes=50, Often=25, Almost Always=0

School Functioning (problems with...)

- Doing the same school activities as peers: Never=100, Almost Never=75, Sometimes=50, Often=25, Almost Always=0
- Missing school/daycare because of not feeling well: Never=100, Almost Never=75, Sometimes=50, Often=25, Almost Always=0
- Missing school/daycare to go to the doctor or hospital: Never=100, Almost Never=75, Sometimes=50, Often=25, Almost Always=0

The scores are derived as follows:

- Mean physical functioning score=sum of all physical function scores / (number of items answered)
- Mean emotional functioning=sum of all emotional functioning scores / (number of items answered)
- Mean social functioning=sum of all social functioning scores / (number of items answered)
- Mean school functioning=sum of all school functioning scores / (number of items answered)

**NOTE: If more than 50% of items in the scale are missing, a domain score should not be computed for that domain.**

Psychosocial Health Summary Score = sum of items in emotional functioning, social functioning, and school functioning scales / (number of items answered)

Physical Health Summary Score = Physical Functioning Scale score (as shown above)

Total score: Sum of all the items / (number of items answered)

### **PedsQL for ages 5-7 years**

The PedsQL response scales are coded as follows:

#### Physical Functioning (problems with...)

- Walking more than one block: Never=100, Almost Never=75, Sometimes=50, Often=25, Almost Always=0
- Running: Never=100, Almost Never=75, Sometimes=50, Often=25, Almost Always=0
- Participating in sports activity or exercise: Never=100, Almost Never=75, Sometimes=50, Often=25, Almost Always=0
- Lifting something heavy: Never=100, Almost Never=75, Sometimes=50, Often=25, Almost Always=0
- Taking a bath or shower by him or herself: Never=100, Almost Never=75, Sometimes=50, Often=25, Almost Always=0
- Doing chores, like picking up his or her toys: Never=100, Almost Never=75, Sometimes=50, Often=25, Almost Always=0
- Having hurts or aches: Never=100, Almost Never=75, Sometimes=50, Often=25, Almost Always=0
- Low energy level: Never=100, Almost Never=75, Sometimes=50, Often=25, Almost Always=0

#### Emotional Functioning (problems with...)

- Feeling afraid or scared: Never=100, Almost Never=75, Sometimes=50, Often=25, Almost Always=0
- Feeling sad or blue: Never=100, Almost Never=75, Sometimes=50, Often=25, Almost Always=0
- Feeling angry: Never=100, Almost Never=75, Sometimes=50, Often=25, Almost Always=0
- Trouble sleeping: Never=100, Almost Never=75, Sometimes=50, Often=25, Almost Always=0

- Worrying about what will happen to him or her: Never=100, Almost Never=75, Sometimes=50, Often=25, Almost Always=0

#### Social Functioning (problems with...)

- Getting along with other children: Never=100, Almost Never=75, Sometimes=50, Often=25, Almost Always=0
- Other kids not wanting to be his or her friend: Never=100, Almost Never=75, Sometimes=50, Often=25, Almost Always=0
- Getting teased by other children: Never=100, Almost Never=75, Sometimes=50, Often=25, Almost Always=0
- Not able to do things that other children his or her age can do: Never=100, Almost Never=75, Sometimes=50, Often=25, Almost Always=0
- Keeping up when playing with other children: Never=100, Almost Never=75, Sometimes=50, Often=25, Almost Always=0

#### School Functioning (problems with...)

- Paying attention in class: Never=100, Almost Never=75, Sometimes=50, Often=25, Almost Always=0
- Forgetting things: Never=100, Almost Never=75, Sometimes=50, Often=25, Almost Always=0
- Keeping up with school activities: Never=100, Almost Never=75, Sometimes=50, Often=25, Almost Always=0
- Missing school because of not feeling well: Never=100, Almost Never=75, Sometimes=50, Often=25, Almost Always=0
- Missing school to go to the doctor or hospital: Never=100, Almost Never=75, Sometimes=50, Often=25, Almost Always=0

The scores are derived as follows:

Mean Physical Functioning=sum of all physical function scores / (number of items answered)

Emotional Functioning=sum of all emotional functioning scores / (number of items answered)

Social Functioning= sum of all social functioning scores / (number of items answered)

School Functioning= sum of all school functioning scores / (number of items answered)

